### Data Collection and Management

2.11

The pre‐intervention data collection period began in May 2023 and continued until the required sample size was reached in January 2024. Following the completion of AI development in the technical sub‐study, we began training nurses and initiated the intervention phase with the corresponding observations and surveys in July 2024. Observations, on‐site wound assessments, and surveys of the nurses are conducted by trained nursing scientists using a digital questionnaire on tablets through the Lime Survey tool (Limesurvey GmbH 2024). The collected data is anonymized and stored on secure, access‐restricted servers available only to the research team.

To ensure that the documentation created can be linked to the observations while maintaining data confidentiality and security, a unique identifier is generated in the AI‐based application and recorded on the observation sheet. Neither this ID nor the data collected during the wound documentation, observation, and survey can be used to identify the patient or nurse. All collected data is stored in a password‐protected folder accessible only to the study team. Consent forms and confirmation of receipt of the voucher are stored securely and are also only accessible to the study team. Upon completion of data collection, the data will be exported and statistically analyzed using SPSS version 28.0.0.0 (IBM Corp 2021). Given the study's small sample size, relatively low complexity, and clearly defined endpoints, the establishment of a data monitoring committee is not deemed necessary.

### Analysis Plan

2.12

Once data collection is complete, we will use multiple linear regression models to examine the effects of the AI‐based digital system on the duration of wound assessment, dressing change, documentation, perceived task load, and guideline adherence. We will calculate an individual linear regression model for each dependent variable and incorporate potential covariates such as the nurses’ professional experience, wound severity, and the general load of the shift. Nominal and ordinal variables (use of the AI demonstrator, severity of the wound, general burden of the shift, and guideline adherence) will be dummy coded. We will then assess each model for linearity, homoscedasticity, and the absence of multicollinearity to satisfy the assumptions of linear regression. If these conditions are met, we will proceed with standard multiple linear regression, incorporating all independent variables as predictors. The f‐test will be used to examine the extent to which the independent variables predict the dependent variable, with R² indicating how much of the variance in the dependent variable can be explained by the independent variables. The t‐test will assess the significance of the predictors. To determine the specific contribution of the use of the demonstrator, we will calculate the explanatory power for both the full regression model and a reduced model without the demonstrator use variable, using the difference in explanatory performance to isolate the effect attributable to the demonstrator use. Datasets with missing socio‐demographic data for nurses, used only to describe the sample and not part of the statistical analysis, will still be included in the analysis. However, datasets with missing values for independent variables will be excluded entirely, and datasets with missing values for dependent variables will be excluded only from the specific model where the data is missing. The significance level is set at 0.05. As this is an exploratory study and a separate model is calculated for each dependent variable, no correction for alpha error is required. To analyze the interrater reliability of the observers, we will use Kendall's rank correlation coefficient (Kendall's tau). To determine the performance of the AI‐based application in the clinical setting, we will calculate its accuracy in predicting wound type and wound classification, using the on‐site assessment of a study team member as ground truth. Additionally, we will descriptively evaluate the usability of both the standard clinical documentation systems and the AI‐based application in terms of central tendency, variability, and distribution.

All statistical analyzes will be performed using SPSS version 28.0.0.0 (IBM Corp 2021).

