### Sample Size

2.6

Based on current methodologies, we performed an a priori sample size calculation using power analysis (Döring and Bortz 2016) with the G*Power 3 software (Faul et al. 2007). For this calculation, we assumed moderate effect sizes between dependent and independent variables (Cohen 1988), an alpha level of 0.05, and a power of 0.80. To test correlations between dependent variables (task load, time, guideline adherence) and four independent variables (use of the demonstrator, general load of the shift, professional experience, severity of wound) using multivariate models (multiple linear regression) under these assumptions, we will require a total of 85 nurses.

With a calculated sample size of 85 nurses and considering up to four independent variables, we anticipate obtaining meaningful results within a manageable timeframe and with the available resources. Accounting for a projected 10% dropout and missing rate, based on experiences from previous studies, we plan to recruit 95 nurses to ensure a sufficiently large sample for subsequent evaluation.

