The selected criteria include performing a finger pressure test or the transparent disk method in the presence of redness (recommendation 9.1), accurately assessing wound type and classification (recommendation 9.2), applying wound edge protection in cases of macerated wound edges or surrounding skin (recommendation 3.1), and ensuring pressure relief for pressure injuries (recommendations 5.1 and 5.5). The response options for these criteria are binary: ‘No’ or ‘Yes or not required’. Sum scores are calculated from the responses, assigning a score of 1 to ‘Yes or not required’ and a score of 0 to ‘No’. Interrater reliability is also measured in the study. Additionally, the nurse's task load during wound assessment, dressing change, and documentation is evaluated using the standardized and validated NASA TLX questionnaire (Human Performance Research Group n.d.).

Other covariates measured include the nurse's professional experience, wound severity, and the general workload of the shift, which is assessed on a 5‐point scale relative to the average.

To assess the accuracy of the AI predictions of wound type and wound classification in the clinical setting, the wound is independently assessed on‐site by a member of the study team, separate from the nurse's assessment and the AI prediction. This assessment serves as the ground truth for calculating the accuracy of the AI predictions regarding wound type and classification.

Additionally, the usability of the documentation systems used, namely the standard clinical documentation systems and the AI‐based digital system, will be assessed in both the control and intervention groups. Usability will be evaluated using the two‐item UMUX Lite questionnaire with a 7‐point Likert scale (Lewis et al. 2013) because of its brevity (Borsci et al. 2020) and comparability with other studies and the SUS scale (Lewis et al. 2013).

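### Guideline adherence is an outcome scored as one sum, but the analysis plan lists it for dummy coding, so its linear regression cannot be run as written

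*Protocol article*

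**What the plan says.** Three sections of the protocol article bear on this.

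- **Section 2.6 (Sample Size)** puts adherence on the outcome side of the model: "dependent variables (task load, time, guideline adherence) and four independent variables". The four independent variables are demonstrator use, shift load, professional experience and wound severity.
- **Section 2.10 (Measures)** defines adherence by five criteria, each answered in a binary format that scores 1 or 0, and then says "Sum scores are calculated from the responses". The range of 0 to 5 is not printed but follows from that scoring.
- **Section 2.12 (Analysis Plan)** assigns each dependent variable its own multiple linear regression, names adherence as one of them, and then says: "Nominal and ordinal variables (use of the AI demonstrator, severity of the wound, general burden of the shift, and guideline adherence) will be dummy coded". The same section requires checks of linearity, homoscedasticity and multicollinearity. It also requires an overall F test, R², t tests of the predictors, and a comparison of explained variance with and without the demonstrator variable.

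**The concern.** Dummy coding is a way to enter a categorical predictor. The other three variables in that sentence are predictors. Adherence is not a predictor in any model the article describes, so the instruction can only act on it as an outcome. There it conflicts with the single sum score of Section 2.10 and with the one-model-per-outcome rule of Section 2.12 itself.

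Better adherence is one of the three benefits hypothesised in Section 2.1. If the text does not fix what the dependent variable is, two analysts could follow the plan in good faith and report different results for it. The study is unblinded and non-randomised, makes no multiplicity correction, and had its control data complete in January 2024. A choice made at analysis would therefore be made with outcome data in hand.

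**Working it through.** **1. The plan's own figure.** Section 2.6 gives "an alpha level of 0.05, and a power of 0.80", four predictors and a moderate effect, with no number for the effect. Assume f² = 0.15. For the overall F test in linear regression, df1 = 4, df2 = N − 5 and noncentrality = 0.15 × N. The smallest N with power of at least 0.80 is 85 (power 0.803). Dropout: 85 / 0.90 = 94.4, rounded up to 95. Both stated figures reproduce. The calculation presupposes one numeric outcome per model.

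**2. What the coding rule does to the outcome.** A 0–5 score has 6 levels.

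- *Full dummy coding:* 6 − 1 = 5 indicator variables. There is then no single dependent variable. The F test, R², demonstrator coefficient and full-versus-reduced comparison of Section 2.12 are not defined for adherence.
- *One 0/1 indicator:* this needs a cut-off, and none is given. The variance of a 0/1 outcome is p(1 − p), so it moves with the mean. In general the homoscedasticity condition then fails whenever the predictors matter.
- *Sum score left alone:* one outcome and one model, as Sections 2.6 and 2.10 imply.

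**3. Does the choice matter?** The documents give no adherence rates, so every input here is an assumption. The setup was n = 85, split 42/43; five independent items; a shift of +0.10 per item in one group, capped at 1; and covariates for experience, 5-level workload and 4-level severity (both dummy coded). All fits were ordinary least squares, testing the group coefficient at 0.05. There were 8,000 null runs for the sum score and 4,000 runs for every other entry.

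| Item rates without the shift | Type I error, sum | Power, sum | Type I error, all five met | Power, all five met |
|---|---|---|---|---|
| all 0.5 | 0.051 | 0.503 | 0.026 | 0.128 |
| all 0.8 | 0.054 | 0.772 | 0.056 | 0.644 |
| 0.6, 0.6, 0.9, 0.9, 0.95 | 0.053 | 0.725 | 0.047 | 0.491 |
| all 0.9 | 0.050 | 1.000 | 0.053 | 1.000 |

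The last row says nothing about power, because the shift takes every item to 1.00. In the third row three items reach the cap. In the first three rows the loss of power is 0.503 − 0.128 = 0.375, 0.772 − 0.644 = 0.128 and 0.725 − 0.491 = 0.234.

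**4. Is linear regression on the sum acceptable?** Its type I error was 0.050 to 0.054. Some fitted value exceeded 5 in 0% to 36% of the null runs, most often near the ceiling, so the model is crude. Its variance is not constant under an effect either. With independent items, 5 × 0.8 × 0.2 = 0.80 against 5 × 0.9 × 0.1 = 0.45. That is a reason for robust standard errors, not for rejecting the model.

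**The case against.** **A consistent reading exists.** In Section 2.12, dummy coded could loosely mean the 0/1 scoring of the five items, just as demonstrator use in the same list is a 0/1 variable. Sections 2.10 and 2.12 would then agree. This is possible but strained. The item scoring is already fixed in Section 2.10, and Section 2.12 names the adherence variable, not its items, beside three predictors. The entry may also be a drafting slip. Nothing in the text settles which.

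**A stronger reading is tempting and does not hold.** A reader might infer that adherence has no valid analysis at all, because a bounded score does not suit linear regression. The simulated type I error contradicts that. Even the linear fit to the 0/1 indicator did not inflate it (0.026 to 0.056). A reader might also infer a known ceiling or a definite inflation of false positives from multiple indicators. The documents give no adherence rates, and indicators cut from one score are mutually exclusive, so a familywise figure that assumes independent tests would not apply.

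**Scope and weight.** What to do if the assumption checks fail is commonly left to a statistical analysis plan, so the missing fallback is not part of this point. The study is an exploratory pilot with several dependent variables and no single primary endpoint, and the other models are untouched. All of this stands and lowers the weight of the point. It does not remove it, because the coding rule is stated in the article and conflicts with other statements there.

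**Conclusion.** The point holds as an internal contradiction. Sections 2.6 and 2.10 define one numeric outcome, and Section 2.12 gives it a coding rule that, applied literally, leaves either five outcomes or one dichotomy without a cut-off. The adherence model is therefore not executable as written.

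Under the assumed rates, the cost of the dichotomised reading is about 13 to 38 percentage points of power. These figures rest on independent items, a +0.10 shift and one particular cut-off (all five met), so they show that the choice matters and do not predict this trial's loss. That the 0/1 version discards information does not depend on the rates.

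The conclusion does not extend to linear regression on the intact 0–5 score, to the other dependent variables, or to the sample size of 85 and 95. It is a wording error with real consequences for one of the three hypothesised benefits, and it should be corrected before the analysis.

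**What to change.** In Section 2.12:

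1. Delete guideline adherence from the list of variables to be dummy coded.
2. State that the dependent variable is the 0–5 sum score of Section 2.10.
3. Specify one model with the same covariates as the others: linear regression with heteroscedasticity-robust standard errors.
4. Add a proportional-odds model on the sum score as a sensitivity analysis. Its drawback is that some score levels may be sparse at about 85 nurses. Adjacent levels may then need collapsing, by a rule set in advance.

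A model of criteria met out of criteria applicable is not a substitute. The response format in Section 2.10 merges fulfilled with not required, so the number of applicable criteria cannot be recovered from those responses.

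The cost is two or three sentences, with no new data and no change to recruitment. Section 2.2 commits the study to updating its registration when the protocol is adjusted, so the clarification belongs there too, with its date and a statement of whether adherence data had been examined by then.

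### The analysis plan reads plain R² as variance explained; with dummy coding on 85 nurses it averages about 8 to 14% when nothing is explained, so adjusted R² should be interpreted instead

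*Protocol article*

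**What the plan says.** The Analysis Plan section of the protocol article specifies a separate multiple linear regression for each dependent variable, with demonstrator use, professional experience, wound severity and shift load entered together. It gives the F-test and the t-tests their roles and then R² its own: "R² indicating how much of the variance in the dependent variable can be explained by the independent variables". Adjusted R² is not mentioned. The demonstrator's own contribution is to be taken from the difference in explanatory power between the full model and a model without that variable.

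The same section sets the coding. Demonstrator use and severity are on a list that ends "general burden of the shift, and guideline adherence) will be dummy coded". Guideline adherence is an outcome, so it adds no predictor column. Professional experience is not on the list. The Measures section gives shift load a five-point scale and gives no number of levels for severity.

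The Sample Size section counts variables, not columns: "With a calculated sample size of 85 nurses and considering up to four independent variables".

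**The concern.** In-sample R² cannot fall when a column is added, whether or not that column is related to the outcome. It is close to the share of variance truly explained only when the columns are few relative to the observations. Here an ordinal variable with L levels takes L − 1 columns, so four variables become considerably more than four columns on 85 nurses.

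What is at stake is the trial's stated summary of how far the independent variables account for duration, task load and guideline adherence. The study calls itself an exploratory pilot and applies no correction for multiple testing, so readers are likely to lean on descriptive magnitudes of this kind. Reading plain R² as variance explained would overstate this one on average.

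**Working it through.** **Inputs**

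- Analysed N: "we will require a total of 85 nurses" (Sample Size).
- Recruited N: 95, after "Accounting for a projected 10% dropout and missing rate" (Sample Size).
- Error rates: "an alpha level of 0.05, and a power of 0.80" (Sample Size).
- Effect size: "we assumed moderate effect sizes between dependent and independent variables" (Sample Size). No number is printed. I assume Cohen's f² = 0.15, which is a population R² of 0.15/1.15 = 13.0%.
- Coding: from the Analysis Plan and Measures sections, as described above.

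**Reproducing the plan's figure.** For the overall F-test with 4 predictors, N − 5 denominator degrees of freedom and noncentrality f²·N, the smallest N with at least 80% power is 85 (power 0.803). Then 85/0.9 = 94.4, which rounds up to 95. Both stated numbers reproduce, and they reproduce with four single-column predictors.

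**Counting columns**

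| Variable | Columns | Basis |
|---|---|---|
| Demonstrator use | 1 | two groups |
| Shift load | 4 | five points, dummy coded, all points used |
| Professional experience | 1 | assumed; not on the dummy-coded list |
| Wound severity | levels − 1 | levels not stated |

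The first three rows sum to 6. Two severity levels give k = 7, four give k = 9 and seven give k = 12. I take 7 to 12 as the range.

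**Mean R² when nothing is explained.** With k columns and no association, R² follows a Beta(k/2, (N − k − 1)/2) distribution, whose mean is k/(N − 1). At N = 85:

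| k | Mean R² |
|---|---|
| 4 (as counted for sizing) | 4/84 = 4.8% |
| 7 | 7/84 = 8.3% |
| 8 | 8/84 = 9.5% |
| 9 | 9/84 = 10.7% |
| 12 | 12/84 = 14.3% |

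At k = 9 the median is 10.1% and the 95th percentile 19.4%. If all 95 recruited nurses were analysed, the mean at k = 9 would be 9/94 = 9.6%.

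**Mean R² at the assumed effect.** Adjusted R² is 1 − (1 − R²)(N − 1)/(N − k − 1). Simulation at N = 85 (400,000 draws) gave:

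| k | True R² 0%: mean R² | mean adjusted R² | True R² 13.0%: mean R² | mean adjusted R² |
|---|---|---|---|---|
| 4 | 4.8% | 0.0% | 17.1% | 13.0% |
| 7 | 8.3% | 0.0% | 20.2% | 13.0% |
| 9 | 10.7% | 0.0% | 22.3% | 13.0% |
| 11 | 13.1% | 0.0% | 24.4% | 13.0% |

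At k = 9 the unadjusted figure is on average 22.3/13.0 = 1.7 times the true value.

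**The demonstrator's R² difference.** This is a one-column comparison. With no association, its mean is 1/84 = 1.2 points.

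**The case against.** The strongest reply is that the bias does not reach the trial's main question. That question is the effect of the application, which is judged by the t-test of the demonstrator and by the full-versus-reduced difference. The t-test and F-test use the correct degrees of freedom, and the difference is inflated by only about 1.2 points. The F-test also stands in the same sentence as R². At 9 columns and 85 nurses an R² below about 19.4% is not significant at 0.05, so a typical null value near 11% would appear beside a non-significant F. All of this stands, and it limits the point to the descriptive reading of the full-model R².

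A second reply is that the article writes only R², that reading it as variance accounted for in the sample is its textbook definition, and that an analysis plan not shown here could add the adjusted value. This stands in part: the article does not exclude adjusted R². But it does fix which statistic is read as explained variance, and as written that statistic is biased upward as an estimate of what the predictors explain beyond this sample.

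A reader might also infer that R² will not be comparable between outcome models. The documents give little support for this. The same predictors enter every model, and records with a missing predictor are dropped from all of them. Only missing outcomes change N between models. Losing five records at 9 columns moves the null mean from 9/84 = 10.7% to 9/79 = 11.4%, and no comparison of R² across outcomes is planned.

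**Conclusion.** The point holds as a minor one. Read as planned, the full-model R² overstates explained variance on average. When nothing is explained, it averages about 8 to 14% at 85 nurses. At a true value of 13%, it averages about 22% with 9 columns. Adjusted R² averages about 0% and 13%.

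The size rests on four assumptions: 2 to 7 severity levels, experience entered as one column, all five shift-load points in use, and f² = 0.15 for a moderate effect. The conclusion does not depend on the upper end of the range, because even 7 columns give 8.3%.

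Two stronger readings are tempting and are not supported. One is that the model certainly has 9 or more columns; that needs at least four severity levels, and the documents give no number. The other is that the trial would report about 11% when there is nothing to find. That figure is an average over samples at 9 columns, and a single result could lie near zero or above 19%. Nothing here shows that a test is invalid or that the demonstrator effect is overstated by anything like 11 points.

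**What to change.** In the Analysis Plan, state that explained variance is interpreted as adjusted R², reported for each model with the number of fitted columns and the analysed N. Give unadjusted R² only alongside the F-test. It would help to state the number of severity levels in the same place, because that number determines the column count.

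The cost is a sentence or two. No data collection, design feature or test changes, and SPSS already prints adjusted R² in the same output table. The article describes intervention-phase data collection as still ongoing, so the wording could be settled before the analysis. The downside is that the reported explained variance becomes less favourable, and adjusted R² can come out slightly negative when little is explained.

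### Shift load, and wound severity if it has three or more levels, is tested only by separate dummy-variable t-tests, so the plan has no single 0.05-level test of either covariate as a whole

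*Protocol article*

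**What the plan says.** The Sample Size section (2.6) sets the number of nurses for testing the outcomes against "four independent variables (use of the demonstrator, general load of the shift, professional experience, severity of wound"). Measures (2.10) says that shift workload is "assessed on a 5‐point scale relative to the average". It lists wound severity as a covariate without giving its number of levels.

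The Analysis Plan (2.12) fits one multiple linear regression per outcome with all independent variables entered. Demonstrator use and wound severity are in the same coding list as "general burden of the shift, and guideline adherence) will be dummy coded". Three assessments follow at the 0.05 level:

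- An F-test and R² describe the whole model.
- The t-test "will assess the significance of the predictors".
- A full model is compared with a reduced one, with demonstrator use as the only variable removed.

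The article names no reference category and no joint test for shift load or severity.

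**The concern.** A t-test on a regression coefficient tests a variable only when that variable occupies one column. After dummy coding, shift load occupies four, and each t-test compares one level with the reference level. Four answers come back to one question, and they depend on which level was left out. The whole-model F-test does not separate shift load from the other variables. The full-versus-reduced comparison would separate it, but it is planned only for the demonstrator. There it adds no new test, because with one column the squared t equals the partial F.

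At stake are statements such as shift load or wound severity being related to duration, task load or guideline adherence. If one is made because one dummy fell below 0.05, its error rate is above the stated level, and another reference category could reverse it. The same would apply in each outcome model.

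**Working it through.** **Inputs.** From the Sample Size section: "an alpha level of 0.05, and a power of 0.80"; "we assumed moderate effect sizes between dependent and independent variables" (no number given; f² = 0.15 is assumed here); four independent variables; and "we will require a total of 85 nurses". Shift load has five levels (Measures). Severity levels are not stated, so 3, 4 and 6 are assumed to show a range. Experience is taken as one numeric column, since it is not in the dummy-coding list.

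**The plan's own figure.** Noncentral F-test of R² with 4 numerator degrees of freedom and noncentrality 0.15 × N: power is 0.797 at N = 84 and 0.803 at N = 85, so 85 reproduces. Allowing for the 10% loss, 85 / 0.90 = 94.4, rounded up to 95, as planned. The four variables were therefore counted as 4 degrees of freedom. What dummy coding does to the power of the whole-model F-test is a separate question, not argued here.

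**Columns after dummy coding.** With L severity levels, p = 1 (demonstrator) + 1 (experience) + 4 (shift load) + (L − 1). For L = 4, p = 9 and the residual degrees of freedom are 85 − 9 − 1 = 75.

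**The two readings compared.**

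- Any-dummy reading: the variable is called significant if at least one of its q t-tests has p<0.05. If the tests were independent, the chance under the null would be 1 − 0.95^q: 0.098, 0.143, 0.185 and 0.226 for q = 2, 3, 4 and 5. They share a reference level and a residual variance, so the true figure is lower and was simulated.
- Joint reading: F = [(R²_full − R²_reduced) / q] / [(1 − R²_full) / (N − p − 1)], where the reduced model drops all q dummies of that variable.

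**Simulation.** N = 85, half the nurses in each phase, normal outcome, no true effects, 8,000 to 10,000 data sets per scenario. The few data sets with an empty level were left out.

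| Variable and assumed shares | Any dummy p<0.05 | Joint F-test | Verdict depends on reference |
|---|---|---|---|
| Shift load, 10/20/40/20/10% | 0.133 to 0.175, by reference level | 0.049 | 0.254 |
| Shift load, equal shares (three runs) | 0.151 to 0.163 | 0.049 to 0.054 | 0.258 to 0.268 |
| Severity, 3 equal levels | 0.086 | 0.047 | 0.094 |
| Severity, 4 equal levels | 0.127 | 0.054 | 0.182 |
| Severity, 4 levels, 40/30/20/10% | 0.134 | 0.051 | 0.168 |
| Severity, 6 equal levels | 0.193 | 0.055 | 0.344 |

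The last column is the share of null data sets in which at least one reference level gives a significant dummy and at least one other does not.

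**Check on the demonstrator.** In one simulated data set its t was −0.793863 under all five shift-load reference levels; t² = 0.630219, equal to its partial F. Its power at N = 85 and f² = 0.15 is about 0.94.

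**Sample size for the joint test.** A 4-degree-of-freedom test of shift load at f² = 0.15 needs N = 85, or 86 if severity has 9 or 10 levels.

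**The case against.** The strongest reply is that neither variable is what the trial is about. The hypothesis in Objectives (2.1) concerns only the AI application. Objectives, Measures and the Analysis Plan all call severity and shift load covariates. This stands, and it limits the point to statements about covariates. It does not remove it, because the Sample Size section lists both among the variables to be tested and the t-test sentence is not restricted to the demonstrator.

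A reader might infer that these variables get no valid test at all. The documents do not support that: each dummy t-test is a valid 0.05 test of its own contrast, and only a test of the variable as a whole is lacking. A reader might also take the 0.13 to 0.17 as the error rate of the plan as written. The plan states no any-dummy rule, and reporting contrast by contrast would avoid that error, though not the dependence on the reference category.

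The number of severity levels is unknown, and with two levels there would be no problem for severity. The shift-load case needs no such assumption.

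The plan waives alpha correction because the study is exploratory and each outcome has its own model. The second reason concerns multiplicity across outcomes, not several tests of one variable within a model.

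Finally, reference categories and joint tests are often left to a statistical analysis plan. That is fair for the reference category. The article does, however, name the test for the predictors, and that test cannot answer the question for a variable with several columns.

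**Conclusion.** The point holds as a minor defect. As written, the method gives no single 0.05-level test of shift load that is independent of the reference category, and none of severity if it has three or more levels. The size, about 0.13 to 0.17 for shift load and 0.09 to 0.19 for severity against about 0.05 for a joint test, rests on the any-dummy reading, on 85 evaluable nurses and on the assumed category shares. The severity figures also rest on an assumed three to six levels. Under the same assumptions the verdict depends on the reference level in about 25 to 27% of null data sets for shift load and 9 to 34% for severity.

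It would be wrong to infer that the test of the AI application is compromised. Demonstrator use is one column, and its estimate and test are the same whichever shift-load or severity level is the reference.

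**What to change.** In the Analysis Plan, replace the t-test sentence with wording to this effect: demonstrator use and professional experience are tested by the t-test of their coefficient; shift load and wound severity are each tested by one partial F-test (R² change) for all their dummy variables together; the reference category of each is named; single dummy coefficients are descriptive. This extends to the two covariates the full-versus-reduced comparison already planned for the demonstrator.

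Alternatively, state that covariate coefficients are for adjustment only and will not be tested, and align the Sample Size wording with that.

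The first option costs one sentence and two block-entry steps per model in SPSS, with no new data and essentially no extra nurses. Its downside is that a covariate may lose a nominally significant category. The Discussion reports that intervention-phase data collection was still ongoing, so the choice can be fixed before the analysis.
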